## Abstract

**Background:**

The citizens’ perspectives on health care are central to the assessment of the health care situation and to regional development. In Germany, however, strategic goals for health care delivery are planned based on population statistics and partly on regional morbidity. Saxony is a German federal state with high average age and low density of physicians which makes the population perspective on quality of health care especially intersting. No existing panel surveys cover issues related to the perceived quality of health care delivery on a regional level in Germany.

**Aim:**

We aim to conduct a longitudinal panel study of the perceived health status and perceived quality of health care of the Saxon citizens as a basis for the systematic derivation of health care goals/measures and target group-specific, regionally suitable prevention measures.

**Methods:**

With an anticipated 15% response rate, 15,000 potential participants have to be contacted to achieve a calculated sample size of about 2,250 participants. The questionnaire will be circulated every other year with the option for adaptations depending on insights of each panel wave. The study protocol was approved by the local ethics committee of the Technische Universität Dresden, Germany (ethical approval code BO-EK-320072022) and has been registered at the German Clinical Trials Register as the German WHO primary registry (study registration number DRKS00031229).

**Discussion and outlook:**

The results are intended to identify gaps in health care and to develop patient-centered health care goals for the region together with stakeholders in Saxon health care planning. At the same time, longitudinal data allow mapping of perceived health status and perceived health care trends.

## 1. Introduction

Perceived attractiveness of a region is determined by how citizens rate their quality of life [1]. Increasing quality of life and attractiveness of a city or region will increase the number of people moving into the area while decreasing the number of people moving out, resulting in the settlement of businesses and cultural facilities [2]. Health status and continuously ensured local health care are prerequisites for a perceived high quality of life [1]. Understanding the citizens’ perspectives on health care delivery is central to the assessment of the health care situation and to regional development throughout the world [3], and the population’s perspective should be taken into account when developing strategic goals for health care delivery [4]. Considering the citizens’ perspectives on health care delivery is also in line with the principles of evidence-based health care and value-based health care. Both concepts stress the importance of patient-centeredness in the assessment of health care structures as well as in the development of health care innovations and when it comes to a quality-orientated renumeration of health care services [5, 6]. A basic prerequisite is the measurement of quality using quality indicators, which necessarily have to include a patient perspective, ideally measured using patient-reported experience measures [7]. In the U.S., reimbursement of health care services based on such quality indicators is already standard practice in many areas and ensures that only high-quality health care services are reimbursed [8]. Taking a wider perspective, patient-centeredness in health care planning is a necessary prerequisite for patient empowerment as one feature of modern health care delivery [9].

In Germany’s federal health care system, however, health care delivery is currently planned solely based on demographics as well as morbidity of certain chronic diseases in a given federal state (§9 section 2 BPL-RL [10]). Although a recent expert statement on the development of health care planning in Germany suggests to consider wait times and travel distances in health care planning [11], the population’s perspective on the availability of doctors, hospitals or other health care facilities, on wait times or on travel distances to health care facilities is still not considered within the federal planning process. These issues, however, are dimensions of quality of health care, covering structural (e.g. availability, distances), process (e.g. waiting times) as well as outcome (experiences made during consultations with health care professionals) quality alike [12]. While some of these domains (availability, distances) can be measured using, e.g., routine data from health care, others can only be assessed by asking (potential) patients directly about them [13].

### 1.1 Rationale

Saxony is one of the German federal states with the highest average age. Of its four million people population, 27% are older than 65 years (reference 2021) and Saxony has the 6^th^ lowest birthrate of all German federal states (1.527 in 2021) [14]. The proportion of the age group older than 65 years is lowest in and around the cities of Leipzig and Dresden and highest in more rural areas, sometimes reaching over 30% (e.g. in the districts of Görlitz, Zwickau, Vogtland, Central Saxony). At least partly, the latter are also the regions where density of physicians and probability of setteling new physicians is lowest [15]. This is of particular importance as the proportion of doctors reaching retirement age in the near vicinity (those who are already over 59 years old) varies between 50% and 75% throughout Saxony [15]. The expectedly decreasing number of physicians meets a growing demand for health care. An increase in the number of patients with diabetes mellitus, hypertension, dementia or oncological diseases is predicted for almost all regions of Saxony [15]. Additionally, Saxony had the 3^rd^ largest death rate of all German federal states, independent of the cause of death (1,480 deaths per 100,000 citizens in 2022) [14].

Panel surveys are longitudinal studies researching the same sample time and again over a potentially open-ended time period. By collecting longitudinal data on the topics raised above, panel surveys allow i) for mapping changes in the assessment of various outcomes at aggregate and individual data levels [16], ii) for avoiding measurement bias due to single points of measurement [17] and iii) for conducting causal analyses on the effectiveness of health care interventions (if intervention and control groups are formed) (see e.g. [18]). Hence, panel surveys contribute to the development of political agendas and their alignment with the reality of citizens’ lives throughout Europe. For example, data from the European Social Survey, which explicitly covers health and well-being every two years, are widely used to assess social determinants of health, which is a prerequisite for targeted social policies [19]. The Health Survey for England, conducted regularly by the NHS, allows e.g., for determining predictors of health care access as well as health outcomes [20]. However, none of the panel questionnaires mentioned above cover issues releated to the perceived quality of health care delivery within a region.

### 1.2 Objective

Therefore, we aim to conduct a structured and longitudinal survey of perceived health status and perceived quality of health care of citizens in Saxony as the first health care panel for Saxony. The panel data can serve as a basis for the systematic derivation of health care goals and target group-specific, regionally appropriate preventive measures and interventions to maintain or improve the quality of care in the region.

The panel’s overarching research questions are:

What is the relationship between perceptions of health status, quality of health care and quality of life?Do individual (health) behavior, use of health care facilities, medical diagnoses, work environment and socio-demographic factors influence perceptions of health status, quality of health care and quality of life?How do perceptions of health status, quality of health care and quality of life change over time?

A general overview of the domains and research questions is depicted in Fig 1.

**Fig 1 pone.0310656.g001:**
[figure not shown]
Domains and research questions. The panel’s research questions are 1) What is the relationship between perceptions of health status, quality of health care and quality of life? 2) Do individual (health) behavior, use of health care facilities, medical diagnoses, work environment and socio-demographic factors influence perceptions of health status, quality of health care and quality of life? 3) How do perceptions of health status, quality of health care and quality of life change over time?

Apart from answering the above listed research questions, our procedure is aimed to be explorative, aiming to shine a light on regional perceptions of quality of life and its predictors and to develop hypotheses to be tested in futher panel waves.

## 2. Methodology

In order to answer the above-mentioned research questions and conduct longitudinal assessments of perceived health status, quality of health care and quality of life in Saxony, we plan to set up a regional health panel in Saxony. The reporting of our methodology follows the PLOSOne_Clinical_Studies_Checklist (see checklist in supporting file S1 File “PLOS ONE Clinical Studies Checklist”).

### 2.1 Domains covered in the questionnaire

The general questionnaire to be used in each wave of the panel will cover the following issues:

perceived quality of life at the region of residence (dependent variable used for studying the influence of perceived quality of health care on quality of life at the region of residence)perceived health status and health problems (perceived health problems and specific diagnoses; predictor for utilization of health care services and perceived quality of health care)utilization of health care services (predictor for perceived quality of health care)perceived quality of health care (predictor for quality of life at the region of residence and central construct of interest of the panel survey)behavioral habits (predictor for perceived health status and utilization of health care services)education, occupation and household status (dimension of living conditions; predictor for utilization of health care services and perceived health status)demographics (insurance and relationship status, gender, age, weight, height; predictor for utilization of health care services and perceived health status)

The complete questionnaire, containing both the questions (n = 48) and the scales, is available as a supplementary file to this publication (see supporting file S2 File “Complete Questionnaire”). Within this file, we also report on the origin of each question, thus demonstrating we only use standardized–not open-ended–questions and mostly rely on previously used and such valid as well as reliable questions. We also explain each question’s anticipated use in subsequent data analyses. Thus, we also reflect on the role each question plays in the overall purpose of our panel study.

### 2.2 Sample size planning

Due to the explorative character of our work, no definitive hypotheses and therefore endpoints can be predefined. Therefore, sample size planning was done based on an exemplary correlation: The sample size was planned to be able to detect an effect of OR = 1.50 with a power of 90% within a regression analysis for a binomially distributed endpoint with a prevalence of 20% and an alpha error of 5% (two-sided). This assumption is based on the example of the Global Activity Limitation Indicator (GALI), used by the EU to measure Healthy Life Years [21], assuming about 20% of the Saxonian population with activity limitations. Sample size was calculated so that this proportion would be reprensented within the sample.

This results in a required sample size of n = 2,196. Assuming a 15% response rate about 14,640 participants (rounded to 15,000) subjects have to be recruited in the first wave.

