### 2.6 Status and timeline

Fig 2 depicts the timeline for the panel survey. The survey is designed as an open-ended project.

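### Sample size and 90% power hold for wave 1 only, and the tests named for change mix real change with panel ageing, selective loss and the regional allocation

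*Protocol article*

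**What the plan says.** Section 2.2 plans for an odds ratio of 1.50 with 90% power, a binary endpoint with 20% prevalence and a two-sided 5% level, and concludes: "This results in a required sample size of n = 2,196". It then turns this into contacts: "Assuming a 15% response rate about 14,640 participants (rounded to 15,000) subjects have to be recruited in the first wave". The abstract gives the expected yield: "15,000 potential participants have to be contacted to achieve a calculated sample size of about 2,250 participants".

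The design is longitudinal. Section 1.1 explains: "Panel surveys are longitudinal studies researching the same sample time and again over a potentially open-ended time period". Section 2.6 adds: "The survey is designed as an open-ended project". The caption of Fig 2 sets waves every two years from 2024, and section 2.4 asks for consent once, for the whole duration. Change over time is research question 3 in section 1.2, and the abstract says that "longitudinal data allow mapping of perceived health status and perceived health care trends".

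For change, section 2.7 plans graphs, ANOVA and t-tests under normality, and otherwise Mann-Whitney or Kruskal-Wallis tests. It names no pairing of a person's answers, no age standardisation and no weighting. Section 2.3 allocates a third of contacts to each of three region types. Section 2.1 lists age among the items collected in every wave. The only recruitment remedy described is advertising if response falls below 15% (section 2.4).

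**The concern.** The sample size stops at the first wave, while the stated purpose depends on later ones. A reader of section 2.2 could take 90% power as a property of the panel, when it describes only the first cross-section.

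The second issue is what a wave-on-wave comparison would measure. If the same people are followed and nobody is added, the survivors are two years older at each wave, the youngest ages empty, people who move into Saxony are not represented, and those who drop out may differ from those who stay. A difference between raw wave means then combines change in Saxony, ageing of the panel and selective loss. The results are meant to inform regional health care goals, so reading such a difference as a Saxon trend could mislead planners. Tests that treat two waves as independent samples also ignore the correlation within persons, which is the main statistical advantage of a panel.

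**Working it through.** **1. The plan's figure.** Inputs from section 2.2: prevalence 20%, OR 1.50, two-sided alpha 5%, power 90%. OR 1.50 applied to 20% gives odds 0.25 × 1.5 = 0.375, so p1 = 0.375/1.375 = 0.2727. The article does not state the distribution of the predictor. With a binary predictor carried by 20% of the sample (assumption; ratio r = 0.25, pooled p̄ = 0.2145):

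n0 = [1.960·√((1+1/r)·p̄(1−p̄)) + 1.2816·√(p0(1−p0) + p1(1−p1)/r)]² / (p1−p0)²
= [1.960·√0.8426 + 1.2816·√0.9534]² / 0.07273² ≈ 1,760.

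The total is 1,760 × 1.25 = 2,200, within 0.2% of 2,196. Contacts: 2,196/0.15 = 14,640, as stated.

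**2. Margin at wave 1.** 15,000 × 0.15 = 2,250. 2,250 − 2,196 = 54, and 54/2,250 = 2.4%. It comes entirely from rounding 14,640 up to 15,000.

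**3. Loss from mortality alone.** Section 1.1 gives 1,480 deaths per 100,000 residents in 2022, or 1.48% a year. If this applied to the panel, 2,250 × (1 − 0.0148)² = 2,184 at wave 2, 2,120 at wave 3 and 2,057 at wave 4. At half that rate, n is 2,217 at wave 2 and 2,184 at wave 3.

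**4. Power for the planning effect.** The article gives no retention rate, so the losses below are assumptions. Power is from the two-proportion calculation in step 1:

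| Loss per wave | n, wave 2 | Power, wave 2 | n, wave 3 | n, wave 4 |
|---|---|---|---|---|
| none | 2,250 | 0.906 | 2,250 | 2,250 |
| mortality only (1.48% a year) | 2,184 | 0.898 | 2,120 | 2,057 |
| 10% | 2,025 | 0.876 | 1,823 | 1,640 |
| 20% | 1,800 | 0.837 | 1,440 | 1,152 |
| 30% | 1,575 | 0.789 | 1,102 | 772 |

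At 20% loss per wave, power is 0.753 at wave 3 and 0.662 at wave 4. A cross-check that does not need the assumed predictor split, Φ((1.960 + 1.2816)·√(n/2,196) − 1.960), gives 0.876, 0.835 and 0.784 at n = 2,025, 1,800 and 1,575.

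**5. Response that would cover the loss.** To keep 2,196 at wave 2 from 15,000 contacts, the response needed is 2,196/((1−d) × 15,000): 16.3%, 18.3% or 20.9% for d = 10, 20 or 30%.

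**6. Ageing.** Waves in 2024, 2026, 2028 and 2030 make survivors six years older at wave 4. If an item such as activity limitation rose by 0.5 to 1 point per year of age (an assumption with no source in the article), ageing among survivors would contribute 6 × 0.5 = 3 to 6 × 1 = 6 points. This shows the possible scale only.

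**7. Allocation.** Table 1 gives large cities, medium-sized cities and municipalities 33.3% each of the sample, against 36.5%, 23.4% and 40.1% of residents. With equal response, an unweighted mean over-represents medium-sized cities by 33.3 − 23.4 = 9.9 points and under-represents municipalities by 40.1 − 33.3 = 6.8 points, at every wave.

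**The case against.** Four points on the other side have force.

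First, the article is condensed. Retention, refreshment and weighting are often left to a fuller document, and nothing says recruitment ends after wave 1. This stands as far as it goes: a reader might infer a closed panel recruited once by design, but the text supports only that no refreshment is described. Section 2.7 does name tests for change, however, so their unsuitability is not a matter of missing detail.

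Second, 2,196 answers a single-wave question in a study that calls itself exploratory. A reader might treat it as the required n for research question 3; it is not. Precision for paired change can hold up well. If 20% of respondents switched status between waves (assumption), the change detectable at 90% power is 3.24 × √(0.2/n): 3.1 points at n = 2,196 and 3.4 at n = 1,800. The first breach also costs almost nothing, at 0.898. What remains is that the 90% is stated without limiting it to the first wave, and that losses accumulate.

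Third, a reader might infer that worsening health will appear in the trend graphs even if nothing changes in Saxony, or that the trends are merely cohort ageing. Neither follows. Deaths among older members and selective loss of the less healthy pull the other way, no direction with age is given for perceived quality of care, and within-person change is a legitimate target.

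Fourth, age is collected and section 2.7 allows appropriate models; t-tests and ANOVA also have paired or repeated-measures forms. That makes the repair easy. But section 2.7 does not specify those forms, and the non-parametric alternatives it names, Mann-Whitney and Kruskal-Wallis, are for independent groups.

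**Conclusion.** The point holds in limited form and is worth correcting. Section 2.2 sizes the first wave and allows no loss, leaving a 2.4% margin at 15% response. The article's own death rate, if applicable to the panel, would use that up by wave 2, or by wave 3 at half the rate. The cost in power is negligible at first and material at losses of 20 to 30% per wave, or as losses accumulate. These figures rest on assumed retention, on response of exactly 15% and on the planning effect; higher response would buy room.

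For the analysis, section 2.7 followed as written gives wave-on-wave summaries that cannot separate period change from ageing and selective loss, that reflect Table 1's allocation rather than the Saxon population, and that may be tested as if the waves were independent samples. The direction and size of the resulting error cannot be derived from the article.

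**What to change.** **Section 2.2.** State that n = 2,196 and 90% power describe the wave-1 cross-section. Add expected n and power at later waves over a range of retention rates, as in the table above.

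**Section 2.7.** For change over time, replace the independent-group tests with a repeated-measures model: a person random effect, wave and baseline age, with a link suited to the item. Report the wave effect as within-person change that includes ageing. Current age and wave should not be entered as if they separated ageing from period: within a person, age is baseline age plus two years per wave elapsed, so the two are collinear.

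Report population trends as a separate quantity. Weight each wave to that year's Saxon distribution of age × sex × region type, and restrict the estimate to ages the panel still covers. Do not present raw wave means as Saxon trends.

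**Cost.** Restated figures and one reweighting step per wave, using age and region already available; no extra recruitment. Intervals widen somewhat. For region type alone, with equal response, the approximate variance inflation is 3 × (0.365² + 0.234² + 0.401²) = 1.05; age and sex weighting would add to it.

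**What this leaves open.** Weighting cannot restore ages that have left the panel, and restating power does not restore n. If n is to be held, refreshment back to 2,250 at 15% response needs 2,250·d/0.15 = 1,500, 3,000 or 4,500 new contacts per wave for a loss of 10, 20 or 30%. Keeping 2,196 at wave 2 through first contacts alone needs 2,196/((1−d) × 0.15) = 16,267, 18,300 or 20,915. Refreshment is the larger undertaking, but it also brings in young adults and newcomers.

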### 2.3 Sampling

A single stage stratified sample will be drawn for the panel. A selection of 16 medium-sized cities in Saxony with at least 15,000 inhabitants in the year 2020 will be represented in the sample. These are expected to experience a particularly sharp decline in available medical care providers, while at the same time forming the spatial planning units for health care provision in Saxony. As a result, rural communities will be slightly underrepresented in the sample.

In addition to 16 medium-sized cities, 16 randomly selected districts of the four large cities Dresden, Leipzig, Chemnitz and Zwickau as well as 16 randomly selected municipalities will be drawn into the sample. Municipalities largely represent rural areas in Saxony and were drawn based on their postal code. In order to ensure a clear differentiation of the area of residence of the participants, municipalities with identical postal codes were not included in the sample. Thus, the final sample is made up from 48 clusters. For each of the 48 clusters formed, 312 to 313 persons will be randomly selected for initial contact. For this purpose, a random sample is requested from the relevant residents’ registration offices for each district or municipality. Administrative fees for drawing the sample are anticipated for some of the registration offices.

Changes in coverage in a particular municipality or district can thus be compared with other municipalities/districts with a similarly large sample. Design effects are estimated to be negligible because the sample clusters cover a fairly large geographic unit.

The sample construction with reference to the Saxon population can be found in Table 1.

**Table 1 pone.0310656.t001:** Sample construction with reference to the Saxon population.

Region	Cluster	Sample	Residents 2020	Portion of region	Portion of sample
**Leipzig**	6	1,875	592,796	14,6%	12.5%
**Dresden**	5	1,562.5	555,459	13,7%	10.4%
**Chemnitz**	3	937.5	245,166	6,0%	6.3%
**Zwickau**	2	625	88,091	2,2%	4.2%
**Large cities**	16	5,000	1,481.512	36,5%	33,3%
**Medium-sized cities**	16	5,000	950,893	23,4%	33,3%
**Municipalities**	16	5,000	1,630,995	40,1%	33,3%
**Sum**	48	15,000	4,063,400	100%	100%

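### The protocol calls the sample single-stage with negligible design effects, but 32 of its 48 areas are drawn at random before persons are, and cluster size and unequal allocation both cut the precision of Saxony-wide estimates

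*Protocol article*

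**What the plan says.** Section 2.3 of the protocol article opens with "A single stage stratified sample will be drawn for the panel". It then describes how areas enter: there is a selection of 16 medium-sized cities, and besides these "16 randomly selected districts of the four large cities Dresden, Leipzig, Chemnitz and Zwickau as well as 16 randomly selected municipalities will be drawn". Within each of the resulting 48 clusters (the protocol's own term), 312 to 313 persons are drawn at random from the residents' registers. On precision it says: "Design effects are estimated to be negligible because the sample clusters cover a fairly large geographic unit". It gives no ICC and no design-effect figure.

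Section 2.2 plans the sample to "detect an effect of OR = 1.50 with a power of 90" percent, for a binary endpoint with 20% prevalence at two-sided 5%: "This results in a required sample size of n = 2,196". The abstract gives the expected yield: "15,000 potential participants have to be contacted to achieve a calculated sample size of about 2,250 participants". Table 1 allots one third of the sample to each of large cities, medium-sized cities and municipalities, whose shares of the Saxon population are 36.5%, 23.4% and 40.1%.

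**The concern.** Selecting areas at random and then persons within them is two-stage sampling. People in the same area may answer alike, and the precision lost depends on two things: how alike they are (the ICC) and how many respond per area. Large areas may lower the first. They do nothing about the second.

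The assumption also fits poorly with the study's purpose. The panel asks about perceived quality of care and quality of life at the place of residence in order to find regional gaps. A truly negligible ICC would mean that localities hardly differ on these outcomes.

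At stake are the intervals around Saxony-wide means and proportions, and tests that compare types of area or use area-level covariates. Section 2.7 makes the analysis primarily descriptive, so such estimates are a main product. The sentence in section 2.3 tells the analyst that no allowance is needed.

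**Working it through.** **Inputs from the protocol.** OR 1.50, power 90%, prevalence 20%, two-sided 5%, n = 2,196 and 15% response (section 2.2); about 2,250 respondents (abstract); 48 clusters and the Table 1 counts (section 2.3).

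**Assumptions.** The ICC is not given; 0.001 to 0.05 is used. The share of respondents with the binary predictor is not given; 20% is used. No finite-population correction is applied to the draw of areas.

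**1. The planned n.** Take 20% as the event rate without the predictor. OR 1.5 gives odds 0.25 × 1.5 = 0.375, so the other rate is 0.375/1.375 = 27.3%. The two-proportion formula with a 20:80 split gives 2,199, or 2,200 in whole groups, within 0.2% of 2,196. Power at 2,196 is 89.96%. The contacts follow exactly: 2,196/0.15 = 14,640. The match at a design effect of 1 is consistent with no clustering allowance in n.

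**2. Slack from rounding.** Respondents per cluster: m = 2,250/48 = 46.9. The margin is 2,250/2,196 = 1.025. Setting 1 + (m − 1) × ICC = 1.025 gives ICC = 0.0246/45.875 ≈ 0.0005. Any larger ICC uses up the margin.

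**3. Weighting, with no ICC needed.** The effect is Σ W²/w, with W the population share and w the sample share. For the three main strata it is 3 × (0.3646² + 0.2340² + 0.4014²) = 0.399 + 0.164 + 0.483 = 1.046, so effective n = 2,250/1.046 = 2,150. With the four large cities as separate strata, the large-city part rises to 0.419 and the total is 1.067, so effective n = 2,109. Both are below 2,196.

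**4. Clustering.** Column A is D = 1 + 45.875 × ICC, with all 48 areas treated as sampled clusters and no weighting. Column B treats the medium-sized cities as fixed strata and applies the three-stratum weights: D = 1.046 + (0.399 + 0.483) × 45.875 × ICC. The half-width is 1.96 × √(0.16 × D/2,250) for a 20% proportion, against 1.65 points at D = 1. The last two columns use A, for a predictor that is constant within areas. Power is for OR 1.5 at effective n 2,250/D (90.6% at D = 1). The naive error is that of a nominal 5% test which ignores clusters, 2 × (1 − Φ(1.96/√D)).

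| ICC | A: D | A: effective n | A: half-width (points) | B: D | B: effective n | Power, area-level predictor | Naive error |
|---|---|---|---|---|---|---|---|
| 0.001 | 1.05 | 2,151 | 1.69 | 1.09 | 2,070 | 89% | 5.5% |
| 0.005 | 1.23 | 1,830 | 1.83 | 1.25 | 1,802 | 84% | 7.7% |
| 0.01 | 1.46 | 1,542 | 2.00 | 1.45 | 1,551 | 78% | 10.5% |
| 0.02 | 1.92 | 1,173 | 2.29 | 1.86 | 1,212 | 67% | 15.7% |
| 0.05 | 3.29 | 683 | 3.00 | 3.07 | 733 | 46% | 28.0% |

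Power for an area-level predictor falls below 80% once the ICC exceeds about 0.008.

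**5. Predictors that vary within areas.** Here D = 1 + 45.875 × ICC of outcome × ICC of predictor. With outcome ICC 0.01 to 0.02 and predictor ICC 0.01 to 0.05, D is 1.005 to 1.05 and power is 90.5% to 89%. At 0.05 for both, D is 1.11 and power 87.5%.

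**The case against.** A reader might infer from the table that the stated 90% power fails. The protocol does not support that. The 2,196 is for a regression odds ratio on an individual endpoint (activity limitation is the example), and the predictors listed in sections 1.2 and 2.1 are mainly individual: behaviour, use of services, diagnoses, occupation, demographics. For these, step 5 shows little loss. Section 2.2 makes no power claim for an area-level predictor.

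Nor is every comparison of areas affected. Section 2.3 wants to set one municipality or district against others. Each named area then has its own random sample of persons, and the difference between areas is the target, not extra error.

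Random selection is stated for only 32 of the 48 areas. The 16 medium-sized cities are described as a selection, with a substantive reason, and may be fixed strata. Column B allows for this, and the result changes little because weighting adds back most of what is removed.

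It can also be said that the design is single-stage if all 48 areas are treated as fixed. That would confine inference to those areas, whereas the protocol speaks of Saxon citizens and relates the sample to the Saxon population.

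The size argument points the right way, since large mixed areas tend to have lower ICCs, and only variation within strata counts. At ICC 0.001 the clustering effect is indeed small. The study is exploratory and its sample size calculation is an example. Survey methods may also be set out in an analysis plan that is not shown, so their absence from section 2.7 is not held against it. What remains is that section 2.3 states a design property that its own description contradicts, and gives a reason that does not establish it.

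**Conclusion.** The point holds for the design label and for the negligible claim. The label is wrong for the districts and municipalities. The claim has no figure behind it and is covered by the planned n only if the ICC is about 0.0005 or less. For state-wide estimates the weighting loss of 1.05 to 1.07 follows from Table 1 without any assumed ICC. The clustering loss, from about 1.05 to 3.3, rests wholly on the assumed range of 0.001 to 0.05.

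Standard errors will be too small only if the analysis ignores clusters and weights and the ICC is not trivial, and then only for Saxony-wide means and proportions, area types and area-level covariates. It would go too far to say that the planned power is lost, that all 48 areas are sampled clusters, or that all area comparisons have inflated error.

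**What to change.** - **Section 2.3:** describe the design as stratified two-stage for the districts and municipalities, and say whether the 16 medium-sized cities are fixed or sampled.
- **Sections 2.2 and 2.3:** replace the negligible claim with the effective n and power over an ICC range of 0.001 to 0.05, together with the weighting effect. Give these separately for individual-level predictors and for state-wide or area-level estimates.
- **Analysis:** for state-wide estimates and comparisons of area types, use design weights with Taylor-linearised, cluster-robust or random-cluster-effect standard errors. Comparisons between named areas need no clustering correction.
- **After wave 1:** report the observed within-stratum ICC for the main outcomes, so that later waves rest on a measured figure.

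The cost is a few sentences and survey or mixed-model commands in place of simple tests. Intervals become wider and the stated precision less favourable. No larger sample is needed, since the study is exploratory and its powered example is little affected.
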